### Randomization and allocation concealment

In this cluster-RCT, recruitment and baseline data collection will be conducted prior to randomization. Cluster randomization, which is necessary for implementation of community-level interventions, mitigates concerns of within-community/village contamination, and improves the feasibility of on-site intervention, will be performed at the community/village level. A total of 20 eligible communities/villages will be randomized using a computer-based random number generator (www.random.org) and assigned to either the intervention group or the control group, with 10 communities/villages in each group. A covariate adaptive procedure will be used to minimize the *P* value from a joint *F* test (1000 iterations) to facilitate covariate balance [34, 35]. Several location level covariates will be considered, including number of village residents, and mean age and sex ratio of residents.

Allocation concealment will be ensured through central randomization [36]. Specifically, an independent statistician will generate a block randomization sequence with randomly permutated block size (4–8) and 1:1 allocation ratio. A sequential list with resulting random numbers will be provided to the study center that recruits villages. Only after participation of a village is confirmed, will the study center reveal labels of the random sequence to the trial team delivering interventions.

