### Sample size

The primary outcome is the improvement of modifiable unhealthy lifestyles, with a reduction by at least one unhealthy lifestyle at 6 months considered a favorable outcome (coded 1) and any other outcome unfavorable (coded 0). According to a previous study, the prevalence of at least one unhealthy lifestyle in Chinese community residents is 89.6% [2, 37]. According to an analysis of the previous two survey waves of the CMEC, it is expected that 2 percent of the control group participants will achieve a favorable outcome. We assume that a 10% percent increase of participants with favorable outcome in the intervention group (to 12% in total) constitutes a minimally important difference.

To achieve a power *of* 0.80 to obtain a statistically significant signal at α <  = 0.05 for p_1_ = 0.02 vs. p_2_ = 0.12 with a chi-squared test of independence, the sample size is estimated as 204 (102 per group). To account for participant attrition of estimated 20%, recruitment target is 128 participants per group, with a total sample of 256 participants for assessment and evaluation.

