### Data analysis

Data analyses will be performed using R version 4.2.1 for Windows. All data will be securely stored in an electronic database and accessible only to researchers who meet the criteria as provided in the research ethics approval document.

Descriptive statistics will be provided for the baseline sample. Categorical variables will be summarized in terms of frequencies and percentage, in total and by intervention group. Continues variables will be summarized as mean ± standard or median (interquartile range) in total and by intervention group.

All main analyses will be performed on intention to treat (ITT) basis. The primary outcome will be analyzed with mixed effects log-linear Poisson regression of any reduction of unhealthy lifestyles at six months (favorable outcome vs not) on intervention group as randomized at baseline [58]. In addition, the model will include a random intercept for subject nested in village and a fixed effect for town (as number of clusters not sufficient for variance estimation in the latter case). Treatment effect at six months (immediately after intervention) will be provided as relative risk ratio [59]. As regards secondary outcomes, reduction of unhealthy lifestyles (favorable outcome vs. not) at all timepoints will be simultaneously analyzed with longitudinal mixed effects log-linear Poisson regression on timepoint, and an interaction term of timepoint and intervention group, with random intercepts for subject nested in village and fixed effect for town as specified for the primary outcome. Other binary outcomes including smoking/drinking quitting, drug intake adherence, frailty will be analyzed in the same fashion. For continuous outcomes including sleep quality, smoking/drinking carving, mental health outcomes, cognitive function, self-efficacy, implicit health attitude, social support, longitudinal analysis of covariance (ANCOVA) models with time and time-group interaction will be estimated, adjusted for the respective outcome at baseline and featuring random intercepts for subject nested in village as well as a fixed effect for town [60]. Estimates of differences in changes in lifestyles between groups at 3, 6, 9, and 12 months will be analyzed post hoc using Wald-tests.

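### Town is a fixed effect in every model described but is not named as a stratum or balancing factor in the village randomisation, which costs about 6 points of power on average if the allocation ignores town

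*Protocol article*

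**What the plan says.** Settings and participants draws 20 communities or villages from four randomly selected towns and does not give the number per town.

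Randomization and allocation concealment assigns 10 villages to each arm and describes two mechanisms. One is a covariate-adaptive procedure based on a joint F test with 1000 iterations, of which it says: "Several location level covariates will be considered, including number of village residents, and mean age and sex ratio of residents". The other is a centrally generated permuted-block sequence with block sizes 4 to 8 and 1:1 allocation. Neither is given a town stratum. The covariate list is open-ended: the three items are examples of what will be considered.

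Data analysis specifies for the primary model "a fixed effect for town (as number of clusters not sufficient for variance estimation in the latter case"). The secondary binary models and the longitudinal ANCOVA models for continuous outcomes carry the same town term.

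Sample size rests on a comparison of individuals: "with a chi-squared test of independence, the sample size is estimated as 204 (102 per group"). It makes no allowance for village or town.

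**The concern.** The analysis always conditions on town, but the allocation is not stated to control it. With a town fixed effect, the treatment effect is estimated from comparisons within towns. A town split 4:1 contributes less information than one split 3:2, and a town that falls wholly in one arm contributes none. With 20 villages in four towns, such splits arise easily by chance. The lost precision could have been kept without recruiting anyone, and it cannot be recovered once the villages are allocated.

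**Working it through.** **The plan's own figure.** Inputs from Sample size: control rate 0.02 ("it is expected that 2 percent of the control group participants will achieve a favorable outcome"), intervention rate 0.12, power 0.80, alpha 0.05 taken as two-sided. With the pooled proportion 0.07:

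n = [1.96·√(2·0.07·0.93) + 0.8416·√(0.02·0.98 + 0.12·0.88)]² / 0.10² = (0.707 + 0.298)² / 0.01 = 101.01, rounded up to 102 per group.

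Allowing for 20% attrition, 102/0.8 = 127.5, so 128 per group and 256 in all. The stated figures reproduce. They contain no term for town.

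**Information with town in the model.** Let n1 and n0 be the villages per arm in a town and n their sum. The information on the arm effect is proportional to the sum over towns of n1·n0/n. Without a town term it would be 10·10/20 = 5. R-squared of arm on town is 1 minus (information/5).

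Assumption: 5 villages in each town.

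- Town-balanced allocation (2:3 or 3:2 in each town): 4 × 6/5 = 4.80, so R-squared is 0.04.
- Allocation ignoring town: mean R-squared is (4 − 1)/(20 − 1) = 3/19 = 0.158, so mean information is 5 × 16/19 = 4.21. The ratio to balance is 4.21/4.80 = 0.877.

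**A whole town in one arm.** There are C(20,10) = 184,756 allocations. A given town lies wholly in a given arm in C(15,5) = 3,003 of them. Inclusion–exclusion over 4 towns and 2 arms gives 8·3,003 − (12·252 + 12·1) + 24 − 6 = 21,006, and 21,006/184,756 = 11.4%.

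**Power.** The town-balanced design is set to 80% as a reference, so power = Φ(2.80·√(information/4.80) − 1.96). Exact enumeration of all 10:10 allocations gives:

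| Information | Share of allocations | Power | Loss (points) |
|---|---|---|---|
| 4.8 | 32.5% | 80.0% | 0 |
| 4.4 | 21.7% | 76.5% | 3.5 |
| 4.0 | 32.5% | 72.5% | 7.5 |
| 3.2 | 8.5% | 62.8% | 17.2 |
| 2.8 | 3.3% | 57.1% | 22.9 |
| 2.4 | 1.3% | 50.8% | 29.2 |
| 1.6 | 0.3% | 36.6% | 43.4 |

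Mean power is 74.1%, a loss of 5.9 points; the median is 76.5%. A loss of 10 points or more has probability 8.5 + 3.3 + 1.3 + 0.3 = 13.4%.

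**Sensitivity.**

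- A t reference with 15 degrees of freedom leaves the result unchanged.
- Unequal towns (3/3/7/7, 3/5/5/7, 4/4/6/6, 2/4/6/8): the mean loss is 5.6 to 7.6 points. The chance of losing 10 or more is 14% to 34%, highest for 4/4/6/6.
- Other reference powers: 50% falls to 44.9%, 60% to 54.3%, 70% to 63.9% and 90% to 85.1%.
- Poisson log-rate scale: 80% falls to 75.8%. At the protocol's own rates with 102 per group, 65.0% falls to 60.8%. The loss is 4.2 points either way.
- Simulated village-level model with town effects (20,000 trials, 10 participants per village): at assumed ICC 0, 0.02 and 0.05, power falls from 76.2% to 69.3%, 69.1% to 62.8% and 61.5% to 54.5%.
- Permuted blocks of 4, 6 or 8 with villages listed town by town: mean power is 77.6%, a loss of 2.4 points.

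**The case against.** The strongest reply is that nothing here is wrong or contradictory. The covariate list is open-ended and town is itself a location-level variable, so the full protocol or allocation script may include it. The permuted blocks give some protection by themselves: if the list runs in town order, the mean loss is only about 2 points. If the named covariates differ between towns, balancing on them may also balance town in part; the article gives nothing from which to judge this. Adjusting for a factor that was not stratified remains a valid analysis.

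All of this stands, and it limits the point. A reader might infer that town is excluded from the balancing. The text does not say so; it only fails to name town. A reader might also take a loss of 10 points as typical. The enumeration does not support that with 5 villages per town: 10 or more is a tail outcome, and about a third of allocations lose nothing. Nor do the documents show which village variable is most prognostic, so no such claim can be made for the baseline lifestyle count.

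What the reply does not remove is the mismatch. Town is the one village-level factor that every described model is certain to use, and nothing in the article commits the allocation to control it. The listing order that would reduce the loss is not stated either.

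**Conclusion.** The point holds as an avoidable loss of precision, not as an error of validity. There is no implication of bias or of an inflated type I error. Under an allocation that ignores town, with 5 villages per town, the expected cost is about 6 points of power. Over the other assumptions checked it ranges from about 2 (blocks in town order) through about 4 (log-rate scale) to about 8 (the least favourable of the unequal splits checked). The chance of losing 10 points or more is about 13% with 5 villages per town and up to about 34% with a 4/4/6/6 split.

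The figures rest on two things that the article does not state: the number of villages per town, and an allocation unrelated to town. The 80% is a reference level for the town-balanced design, not an estimate of this trial's power. The change is worth making because it needs no extra participants, and because the sample size carries no margin for town.

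**What to change.** Stratify the village randomisation by town. Alternatively, restrict the candidate allocations in the covariate-adaptive procedure to those in which the arm counts differ by at most one within every town and the overall split is 10:10. Keep the town fixed effect in the models, and state the number of villages per town.

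As an option, add the village mean baseline number of unhealthy lifestyles to the balance set. Randomization and allocation concealment and Timeline of data collection both place baseline data collection before randomisation, so it will be available.

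The cost is a small change to the allocation script and fewer admissible allocations. With 5 villages per town, C(4,2) × 10⁴ = 60,000 of the 184,756 allocations remain. With 4/4/6/6, 6 × 6 × 20 × 20 = 14,400 remain. Covariate balancing narrows the set further, so check that enough distinct allocations are left among the 20 clusters. The change must be in place before the villages are randomised.

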### Data collection and outcomes

Questionnaires and scales will be administered in onsite face to face interviews at baseline, 3, 6, 9, and 12 months. Face to face interviews will be conducted by trained research assistants (students). Physical examinations will be conducted by community doctors with at least 5 years of clinical experience. Biological samples such as blood and stool samples will be collected by trained nurses and delivered to specialized laboratories with procedures to keep the cooling chain and avoid contamination.

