#### Primary outcomes

The primary outcome is the reduction of modifiable unhealthy lifestyles immediately after intervention (6 months). Unhealthy lifestyles considered comprise smoking, excess alcohol consumption, physical inactivity, unbalanced diet, and overweight/obesity (representing balance between energy intake and energy expenditure). Items as formulated in the Healthy Lifestyle Index Score (HLIS) from the European Prospective Investigation into Cancer and Nutrition cohort study [41], will be used to measure these lifestyles (see Table 2). Assessment of body mass index (BMI) and categorization into overweight/obesity will rely on relevant recommendations according to Chinese guidelines [42], while dietary index is based on the Mediterranean Diet Score [43]. For reasons of simplicity each lifestyle will be coded as a dichotomous variable with 0 indicating absence, 1 indicating presence of a particular unhealthy lifestyle. The decrease of unhealthy lifestyles by at least one at 6 months is considered favorable.

**Table 2 Tab2:** Components of lifestyle risk score

Components	Score	Measurement	Definitions in the study
Smoking status	0–4	Questionnaire • History of smoking in the past	Never = 4, ex-smokers quit > 10 years = 3, ex-smokers quit ≤ 10 years = 2, current ≤ 15 cigarettes/day = 1, current > 15 cigarettes/day = 0 [41]
Alcohol intake	0–4	Questionnaire • Alcoholic beverage consumption per day	low consumption of alcohol (< 6.0 g/day = 4, 6.0–11.9 g/day = 3, 12.0–23.9 g/day = 2, 24.0–59.9 g/day = 1, 60 + g/day = 0) [41, 44]
Physical activity	0–4	International Physical Activity Questionnaire • Number of hours per week spent in moderate to vigorous activities, vigorous-intensity PA	Metabolic equivalent tasks for four activity domains (occupational PA; transportation PA; PA for housework; sports and leisure-time PA): fifth quintile = 4, fourth quintile = 3, third quintile = 2, second quintile = 1, first quintile = 0 [41]
Dietary factors	0–4	Food Frequency Questionnaire • MDS, a linear score that incorporates 9 nutritional components of the Mediterranean diet [45]	Scoring 4 to 0 points for top to bottom quintile of the MDS: fifth quintile = 4, fourth quintile = 3, third quintile = 2, second quintile = 1, first quintile = 0 [44]
Overweight/obesity	0–4	Medical examination • BMI	< 22 = 4, 22–23.9 = 3, 24–25.9 = 2, 26–27.9 = 1, ≥ 28 = 0 [46]
Total score	0–20	Total of unweighted five components	

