### Timeline of data collection

Participants who meet the inclusion criteria will undergo baseline data collection given informed consent. Communities will only be randomized after this baseline data collection, with corresponding allocation of participants to experimental or control group. Demographic characteristics and medical records data will respectively be surveyed and extracted at baseline. Primary outcome and secondary outcomes assessed with questionnaires and scales will be collected at five measurement points: baseline, 3 months after baseline, primary end-point. That is end of instructed intervention period (6-month follow-up), 9-month follow-up, and 12-month follow-up. Laboratory data will be collected at four time points: baseline, 3 months, primary end-point (6-month), and 12-month follow-up (Fig. 3).

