## Discussion

Evidence suggests that approximately 90% of Chinese and over 90% of European adults exhibit at least on unhealthy lifestyle behavior including smoking, alcohol consumption, physical inactivity, unbalanced diet and obesity, with higher prevalence found for adults living in less economically developed areas [2, 65]. These unhealthy lifestyles often cluster and have additive or synergistic effects, increasing the risk of chronic disease and multimorbidity [66]. Recent advances in mHealth provide an appealing and cost-effective approach to intervention targeting the reduction of unhealthy lifestyles. To date, only a few mHealth studies using multiple-level lifestyle interventions at multi-levels have been conducted in community-based population, all in the USA [24, 25, 67]. So far respective studies in Chinese community residents have not been reported.

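### Neither the allocation nor the primary model uses participants' baseline unhealthy-lifestyle count, although it is known before randomisation and limits who can succeed

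*Protocol article*

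**What the plan says.** Under Randomization and allocation concealment, the protocol article allocates 20 communities or villages, "with 10 communities/villages in each group", and describes the balancing factors as follows: "Several location level covariates will be considered, including number of village residents, and mean age and sex ratio of residents". All three named factors describe the location and its whole population.

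The same section states that "recruitment and baseline data collection will be conducted prior to randomization". Timeline of data collection agrees: "Communities will only be randomized after this baseline data collection, with corresponding allocation of participants to experimental or control group". Data collection and outcomes adds: "Questionnaires and scales will be administered in onsite face to face interviews at baseline, 3, 6, 9, and 12 months". The lifestyle items are therefore in hand for every enrolled participant when villages are allocated.

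The primary outcome is binary: "The decrease of unhealthy lifestyles by at least one at 6 months is considered favorable". The participant inclusion criteria do not require an unhealthy lifestyle at entry.

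Under Data analysis, the primary model contains arm, town as a fixed effect, and random intercepts. The adjusted model under Sensitivity analysis adds age and gender. Neither contains the baseline count. For continuous secondary outcomes, by contrast, the same section does adjust for the baseline value of the outcome.

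**The concern.** The people analysed are about 13 per village, selected by age, participation in two cohort waves and smartphone access. The age and sex mix of all residents is a weak stand-in for so small and selected a group, and says little about how many unhealthy lifestyles its members have.

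That number sets the room for success. Someone with none cannot improve, and someone with several has several ways to improve. If one arm happens to start with more unhealthy lifestyles, its expected success rate is somewhat higher even when the intervention does nothing. The plan holds the information needed to prevent this, yet as described uses it neither at allocation nor in the primary analysis. Balancing cannot be added once the villages are allocated.

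**Working it through.** **1. The plan's own figure.** For 2% against 12%, two-sided 0.05, power 0.80, pooled variance (mean rate 0.07):

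n = [1.960 × √(2 × 0.07 × 0.93) + 0.842 × √(0.02 × 0.98 + 0.12 × 0.88)]² / 0.10² = (0.707 + 0.298)² / 0.01 ≈ 101.0, rounded up to 102 per group. Then 102 / 0.80 = 127.5, so 128 per group and 256 in all. The stated sample size reproduces, and nothing below changes it.

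**2. Inputs for the imbalance.**
- From the article: 20 villages, 10 per arm, 256 participants, so 256 / 20 = 12.8 per village; 89.6% with at least one unhealthy lifestyle, so about 10.4% with none.
- Assumed, because the article does not give them: ICC of the baseline count (0.01 to 0.10 in step 3, 0.02 to 0.10 in step 4); count with mean about 1.9 and SD 1.1, which puts about 10 to 11% at zero; resident covariates correlated 0.5 with the village effect.

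**3. Closed-form check in SD units.** If balancing on resident factors did nothing for the count, the standardised arm difference has SD = √[(2 / 128) × (1 + 11.8 × ICC)].

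| ICC | Design effect | SD of arm difference | Chance of more than 0.25 SD |
|---|---|---|---|
| 0.01 | 1.118 | 0.132 | 6% |
| 0.05 | 1.590 | 0.158 | 11% |
| 0.10 | 2.180 | 0.185 | 18% |

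**4. Simulation with balancing.** Villages of 13 were simulated, and the best-balanced of 1000 random 10:10 splits was chosen, for ICC 0.02 to 0.10.

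| Balancing set | SD of arm difference in mean count | Chance of more than 0.2 lifestyles |
|---|---|---|
| Resident factors only | about 0.14 to 0.19 | about 17 to 29% |
| Plus participants' village mean count | 0.02 to 0.03 | about 0% |

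**5. Effect on the primary contrast under no intervention effect.** Take the chance of success as 1 − (1 − q)^count, with q set to give the overall rate.
- At 2% (q about 0.011), a 0.2 difference in count shifts the contrast by roughly 0.2 × 2% / 1.9 ≈ 0.2 points. Over all allocations the shift has SD 0.16 to 0.20 points.
- At 12%, the same proportional arithmetic gives 0.2 × 12% / 1.9 ≈ 1.3 points, and the count model itself about 1.2. Over all allocations the SD is 0.9 to 1.1 points.

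For scale, the sampling standard error of the difference with 128 per arm, ignoring clustering, is √(2 × 0.02 × 0.98 / 128) = 1.75 points at 2% and √(2 × 0.12 × 0.88 / 128) = 4.06 points at 12%. As a share of that variance, the imbalance is about (0.20 / 1.75)² ≈ 1% at 2% and at most (1.1 / 4.06)² ≈ 7% at 12%.

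**6. Effect on the risk ratio.** If the arms differ only in the share able to succeed, a 5-point gap around 89.6% multiplies the ratio by 0.921 / 0.871 ≈ 1.06, and a 10-point gap by 0.946 / 0.846 ≈ 1.12. The planned ratio is 0.12 / 0.02 = 6.0.

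**The case against.** The strongest reply is that this is ordinary randomisation error. It favours either arm with equal chance and is already part of the sampling variance. Even with an ICC of zero the SD of the count difference is about 0.137, so most of the imbalance comes from having 256 individuals rather than from having 10 villages per arm. At the protocol's own 2% control rate the shift is negligible beside 10 points. All of this stands, and it fixes the size of the point.

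The covariate list is also open-ended, so a fuller document may name more factors. That stands in part. But the listed factors are expressly location level, and the model as described omits the count too. Using it is a better rule, not a missing detail.

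Three stronger readings are tempting and are not supported:
- A reader might infer that the trial is biased. Allocation is random with respect to the count, so the estimate is not systematically shifted.
- A reader might call the count the strongest predictor of the primary outcome. The article gives no ranking of predictors. It supports only that a count of zero cannot fall.
- A reader might want urban or rural site type balanced because the Discussion reports unhealthy lifestyles "with higher prevalence found for adults living in less economically developed areas". That sentence concerns economic development among Chinese and European adults, not communities against villages within the four study towns, and the model already has a term for town.

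Finally, the balancing text needs repair of its own. It says "A covariate adaptive procedure will be used to minimize the" P value of a joint F test, which taken literally selects imbalance, and the next paragraph describes permuted blocks. The simulation in step 4 assumes the evident intention, a search for good balance. Correcting that wording leaves the choice of covariates open.

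**Conclusion.** The point holds as one of avoidable chance imbalance and a modest loss of precision. The article names only whole-village factors for balancing, has the participants' baseline counts available at allocation, defines an outcome that those counts limit, and describes a primary model without them.

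There is roughly a 17 to 29% chance that the arms differ by more than 0.2 unhealthy lifestyles. A gap of that size is worth about 0.2 percentage points at the planned control rate and about 1 point at a rate near 12%. Neither threatens a true difference of 10 points. It would count for more if the real effect were smaller or the background rate of improvement higher than planned.

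These figures rest on the assumed ICC, count distribution, correlation with resident factors and near-equal village sizes. The direction and the gain from including the count hold across the range examined. The change is worth making because it is nearly free and the allocation half of it cannot be made later.

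**What to change.** 1. **Randomization and allocation concealment:** add the village mean baseline number of unhealthy lifestyles among enrolled participants to the balancing covariates. Preferably use the enrolled participants' mean age and sex ratio as well, in place of the residents' values.
2. **Data analysis:** add the participant's baseline number of unhealthy lifestyles as a covariate in the primary model, as the plan already does with the baseline value for continuous outcomes. Both halves are needed: balancing on a factor that the analysis ignores leaves the standard error larger than it should be.
3. **In the same edit,** reconcile the wording that minimises the joint-F P value with the permuted-block description, so that a single allocation procedure is stated.

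Cost: no new participants, visits or measurements, and no change to the stated sample size. The balance step uses a few more columns of data already collected, and the model has one more term. With more covariates, the best of 1000 allocations balances each of the others slightly less tightly.

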##### Recruitment method

The community/village is confirmed by the governmental committee of the town (after having been randomly selected), then preliminary screening of candidate participants will be conducted.

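### The study center that recruits villages receives the allocation list and also reveals the arm labels, so concealment from the recruiter is not secured as written

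*Protocol article*

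**What the plan says.** The section Randomization and allocation concealment makes the claim: "Allocation concealment will be ensured through central randomization". It then describes the mechanism in three steps.

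- Generation: "an independent statistician will generate a block randomization sequence with randomly permutated block size (4–8) and 1:1 allocation ratio".
- Custody: "A sequential list with resulting random numbers will be provided to the study center that recruits villages".
- Release: "Only after participation of a village is confirmed, will the study center reveal labels of the random sequence to the trial team delivering interventions".

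On timing, the same section states that "recruitment and baseline data collection will be conducted prior to randomization", and Timeline of data collection repeats that communities are allocated only once baseline data are in. Settings and participants gives the reverse order: the 20 villages are drawn at random, then randomized, and adults in them are screened and invited afterwards.

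On entry of villages, Recruitment method says: "The community/village is confirmed by the governmental committee of the town (after having been randomly selected"), with preliminary screening of candidates to follow. The site criteria also require the local committee's agreement and at least 5 eligible residents.

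**The concern.** Allocation concealment protects against the party that brings units into the trial. That party must not know the next assignment while it can still affect which unit enters, when it enters, or who is enrolled within it. In this plan the recruiting center receives the sequence and is also the party that discloses the labels. The one safeguard stated keeps the labels from the team delivering the interventions, and that team is not described as recruiting villages.

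If the center knew a village's arm early, it could influence the order or timing of confirmation. Under the order in Settings and participants, it could also influence which adults are screened and invited. With 20 villages, 10 per arm, a few influenced entries could matter, and selection of this kind cannot be reliably repaired in the analysis. The trial would also report a concealment property that its described procedure does not guarantee.

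**Working it through.** The plan gives no figure on this point, so the check is a reading of the passages side by side.

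**1. Who holds what.**

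| Step | Party named | Source |
|---|---|---|
| Generate sequence | Independent statistician | Randomization and allocation concealment |
| Receive sequential list | Study center that recruits villages | Same section |
| Reveal labels | The study center | Same section |
| Receive labels after confirmation | Team delivering interventions | Same section |
| Hold the label key before confirmation | Not stated | – |

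A party can reveal only what it holds or can obtain. The statistician has no described role after generating the sequence, and no other key-holder is named. The natural reading is that the center has access to the key. The text does not say so, and it does not say the opposite.

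**2. Whom the restriction covers.** The release sentence limits when the delivery team learns the labels. No sentence limits when the recruiting center learns them.

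**3. Whether the order of steps removes the problem.** If all 20 villages and their participants were enrolled and measured before any assignment existed, custody of a list could not steer recruitment. Two places in the article state that order. Two features work against it:

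- A sequence in permuted blocks, with labels released once a given village is confirmed, describes assignment village by village from a list made beforehand. It does not describe one draw after all villages are in.
- Settings and participants randomizes the villages first and screens adults afterwards.

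**4. Whether changing the custodian alone would be enough.** Suppose the key were withheld until each confirmation. A center that reveals labels one at a time would still know all past assignments. As an illustration, assume blocks of 4, 6 or 8 with equal probability (the article says only 4–8), and guess the arm that is behind so far, at random when tied. In simulated sequences of 20 villages this guess was right about 67% of the time, against 50% with no information. This does not measure the bias in this trial. It shows only why simultaneous release is better than sequential release.

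**5. Size.** The article gives no between-village variation in the primary outcome and no probability that a village would be steered. A bias in the treatment effect therefore cannot be computed from it.

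**The case against.** The strongest case on the other side has four parts.

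- **The list is not described as labelled.** The text separates random numbers, handed over first, from labels, disclosed later. Issuing codes before labels is a recognised concealment device. This stands. A reader might infer that the recruiter can read off the next village's arm, or that all 20 assignments are known in advance. The document does not state either, and both depend on the center holding the key early.
- **Villages are not picked freely by the recruiter.** They are drawn at random and confirmed by the town's committee, and no discretionary replacement is described. This stands and narrows the route to bias. It does not close it, because entry still depends on confirmation, local agreement and enough eligible residents, and the order and timing of those steps are not fixed.
- **Recruitment and baseline come before randomization.** Under that order the harm largely disappears, so a reader should not infer that custody is a flaw whatever order is used. The same section also describes a covariate-balancing procedure over the 20 villages. If that alone set the allocation, no pre-issued list would fix the next arm. Both points stand, but the article does not hold to either arrangement consistently.
- **A condensed article may leave key custody to the full protocol.** That would excuse silence. Here the article does describe custody, and what it describes does not deliver the central randomization it claims.

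**Conclusion.** The point holds in limited form. The article gives the sequence to the recruiting center, makes that center the discloser of labels, and restricts only the delivery team's access. Concealment from the recruiter is therefore not secured as written, and the description fits poorly with central randomization.

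A reader might conclude that concealment does not exist. The document does not support that: labels are kept from the delivery team until confirmation, villages are drawn at random, and two sections place enrolment before allocation. The last protection is unreliable while the sections disagree on the order.

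The conclusion rests on one inference, that a center which reveals labels can obtain them beforehand. If another party in fact holds the key until recruitment and baseline are complete, a sentence saying so settles the custody question. No magnitude of bias is claimed.

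**What to change.** In Randomization and allocation concealment, replace the sentence that gives the list to the recruiting center. State instead that the independent statistician keeps both the sequence and the label key, and releases all 20 assignments at once, directly to the delivery team, after the last village is confirmed and its baseline is complete. State that the recruiting center holds neither. Because Blinding keeps the trial's statisticians blinded, make clear that the key-holder is not one of those who analyse the data.

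Rewrite Settings and participants so that its order of steps agrees with Randomization and allocation concealment and with Timeline of data collection.

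The cost is small. The independent statistician already exists, and baseline is already meant to come first in two sections. The one practical downside is that villages confirmed early must wait for the last one before the intervention starts.
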